## Abstract

**Supplementary Information:**

The online version contains supplementary material available at 10.1186/s13063-023-07762-7.

## Introduction

### Background and rationale

Highly effective interventions against malaria vectors that preferentially feed on humans late at night and rest inside houses have been developed and implemented at scale. Their effectiveness is a function of the fact that they specifically target indoor-biting and indoor-resting mosquitoes, which are often the same mosquito species comprising the bulk of the vectorial system.

However, several mosquito species have evolved high levels of resistance to the insecticides used in long-lasting insecticide-treated nets (LLINs) and indoor residual spraying (IRS) as a result of prolonged exposure through the scale-up of these interventions. There is increasing concern that this insecticide resistance is undermining the effectiveness of these interventions. Furthermore, malaria vectors exhibit different behavioral characteristics, such as outdoor and daytime biting, that compromise the effectiveness of existing vector control strategies.

In addition to the biological need for female *Anopheles* species to take a blood meal to obtain the protein necessary for egg production, all *Anopheles* must feed regularly and frequently on liquid and carbohydrates (sugars) to survive. Mosquitoes are guided to sugar sources by chemical attractants. The ATSB (Attractive Targeted Sugar Bait) is designed specifically to attract the mosquito with a source of liquid and sugar and includes an ingestion toxicant to then kill the mosquito. Using sugar sources to attract mosquitoes to an ingestion toxicant is a relatively simple and inexpensive strategy that has been shown to be highly efficacious for mosquito control in a limited number of trials.

Westham Co. developed a bait station that contains a plant-based mosquito attractant, sugar as a feeding stimulant, and an active ingredient (the neonicotinoid, dinotefuran) to kill the foraging vectors. The bait additionally contains a commonly used bittering agent called Bitrex (https://www.bitrex.com/en-us) that deters mammalian consumption of the bait. The bait station has a protective membrane that covers and protects the bait from rain and dust, but that allows mosquitoes to feed through it (see Fig. 1). Durability studies conducted in Mali, Kenya, and Zambia in 2019–2021 showed that the Westham ATSB can remain effective in the field for at least 6 months. The protective membrane allows mosquitoes to feed, but it serves as a barrier to pollinators. Field studies to-date have shown that the ATSB has a minimal impact on non-target organisms. This includes evidence specifically for the toxicant that will be used, dinotefuran. An initial environmental assessment and subsequent field trials in Mali have demonstrated that when deployed within the ATSB, the toxicant does not pose safety risks to non-target organisms, including pollinators and humans (unpublished data, personal communication with [name]).

**Fig. 1 Fig1:**
[figure not shown]
ATSB design

The Westham ATSB was selected based on results from early testing of bait stations in Israel and Mali. In these studies, bait stations with a food dye marker (without toxin) established that large proportions (> 25%) of the mosquito population were marked daily by the food dye [1]. Proof of concept studies for the impact on mosquito vectors in Mali began in 2015 with a collaborative team from Hebrew University, University of Bamako, University of Miami, Tel Aviv University, and University of Haifa. Research beginning in early 2017 incorporated the toxicant dinotefuran into the bait stations. Early entomological results indicate that outdoor use of ATSBs reduces vector abundance and skews the adult age distribution towards younger mosquitoes which are not infective [1, 2]. Field studies in Mali concluded in early 2018 demonstrated the impact of the ATSB on entomological measures and established an optimal deployment pattern for the local setting [1, 2]. This deployment protocol of two ATSBs installed on opposite exterior walls of sleeping structures at a height of 1.8 m was associated with a target mosquito daily feeding rate of at least 30%. The drastic reduction in mosquito density, particularly of older females, proportion of sporozoite-infected females, and entomological inoculation rate suggest that the ATSB can significantly reduce malaria parasite transmission [2].

Modeling of entomological ATSB study data suggests that ATSBs could markedly reduce mosquito populations across a range of different transmission intensities and should have great potential when used in combination with other indoor vector control tools.

The World Health Organization Vector Control Advisory Group (VCAG) reviewed these data and recommended the evaluation of the potential of the Westham ATSB to reduce clinical malaria incidence in different transmission settings in sub-Saharan Africa. This SAP is intended to serve as a master SAP for each of three trial sites in Kenya, Mali, and Zambia. Three harmonized clinical trials will use this master plan as the basis for site-specific SAPs which may contain minor modifications to adhere to site-specific nuances, including but not limited to, changes in covariables included in analysis or definitions and cutoffs of said variables and summary measures. While the intent of the harmonization is to largely ensure that the trial analysis is conducted comparably and identically, the site-specific SAPs will require minor modifications [3].

## Research questions and hypotheses

### Primary research question

Is outdoor deployment of ATSBs plus universal vector control coverage (LLIN or IRS) more effective than universal vector control coverage alone at reducing cohort-based clinical malaria incidence over a 2-year period?

### Secondary research questions

(2)Is deployment of ATSBs associated with a reduction in community parasite infection prevalence?(3)Is deployment of ATSBs associated with a reduction in passively detected confirmed malaria case incidence?(4)Is deployment of ATSBs associated with a decline in malaria vector abundance (particularly among older females), longevity of vector mosquitoes (parity status), sporozoite rates, and EIR?(5)What are the barriers to high ATSB coverage?(6)Does ATSB deployment affect LLIN use?(7)What is the cost and cost-effectiveness of outdoor ATSB deployment as a vector control intervention?

## Description of research objectives

### Primary objective

To evaluate the efficacy of ATSB deployment in the context of universal vector control coverage (IRS or LLIN) coverage after two transmission seasons in population-based cohort clinical malaria incidence as compared with universal coverage with standard vector control alone.

### Secondary objectives

(2)To evaluate the efficacy of ATSB deployment in the context of universal vector control coverage (IRS or LLIN) on community parasite infection prevalence as compared with universal coverage of vector control alone.(3)To evaluate the efficacy of ATSB deployment in the context of universal vector control coverage (IRS or LLIN) on passively detected confirmed malaria case incidence as compared with universal coverage of vector control coverage alone.(4)To assess a minimum set of entomological outcomes (parity, mosquito abundance, human landing rate, entomological inoculation rate) that measure ATSB efficacy in reducing the target vector population and transmission.(5)To assess the acceptability of ATSBs by communities and other stakeholders. This includes the identification of potential barriers to uptake and consistent ATSB coverage, together with an assessment of ATSB impact on coverage and use of existing malaria control interventions (e.g., LLIN use, treatment-seeking behavior).(6)To estimate the cost and cost-effectiveness of deploying ATSBs for malaria control.(7)To assess the safety of ATSBs on humans by monitoring adverse effects in communities where ATSBs are deployed compared to the control.

## Study methods

### Trial design

An open-label two-arm cluster randomized controlled trial (CRCT) design will be used comparing ATSB + universal coverage with a WHO core VC intervention vs universal coverage with VC alone (in the context of other standard-of-care malaria interventions appropriate to the local context including case management, administration of vaccines, seasonal malaria chemoprophylaxis, where applicable). The trial will follow a group-sequential design [4] with one (two in Kenya) potential interim analysis. Three stand-alone superiority CRCTs will be conducted, one in each of Kenya, Mali, and Zambia with design and methods standardized across sites. Each trial is expected to have sufficient power (≥ 80%) to answer the primary research questions in that setting. Universal VC (mainly using LLIN) will be ensured in both arms prior to the start of the study. The intervention arm A will receive ATSBs for up to 2 years. The control arm B will receive universal vector control coverage. Both study arms will receive any other standard-of-care malaria control and prevention interventions such as treatment of uncomplicated malaria with artemisinin combination therapies which may vary from location to location (e.g., including seasonal malaria chemoprophylaxis and RTS,S vaccination in some sites).

### Randomization

Restricted randomization was used to allocate study clusters to intervention and control arms with a balance between study arms on key baseline characteristics, including the primary outcome. Steps one through seven below were carried out by an independent statistician in collaboration with a member of the study team who was *not* responsible for trial implementation. Randomization was conducted independently for each trial. The steps for randomization are as follows:Establish balance criteria. The factors described in Table 1 below may be considered for suitability as restriction criteria. This list is suggestive rather than prescriptive and specific criteria and restriction limits will vary by study site. Criteria for determining balance will be varied during the restricted randomization process to both ensure balance and the validity and lack of bias in study design. In the Zambia site for example, randomization lists were designed to include balance on malaria prevalence by RDT, whether or not entomological data collection was to be conducted in the cluster, bed net use reported in a baseline cross-sectional survey, and the use of indoor residual spraying in the cluster.Generate a list of at least 100,000 randomizations (Allocation sequences)Check randomizations (allocation sequences) against balance criteria and drop those that do not meet balance criteriaAssess the number of randomizations (allocation sequences) remaining. If fewer than 10,000 acceptable randomizations (sequences) remain, stop and relax restriction criteria. If a high proportion of allocation sequences remain (e.g., > 90%), consider tightening balance criteria.Test the remaining set of potential randomizations (allocation sequences) for validity, specifically that all clusters are being independently assigned to study arms (i.e., check that no two clusters are disproportionately jointly assigned to the same or disproportionately to opposite arms).Randomly choose a randomization (allocation sequence).Flip a coin to determine if arm A or arm B is ATSB or control.

**Table 1 Tab1:** Covariates to be considered for restricted randomization

Covariate/endpoint	Restriction criteria	Data source	Analytic method
Malaria disease incidence	Difference in mean baseline clinical case incidence between trial arms (size of difference to be assessed when data are available)	Baseline cohort	Difference in baseline disease incidence of cluster summaries between study arms
Bednet use	Difference in mean proportion of persons slept under any net night before survey between trial arms ≤ 5 percentage points	Baseline survey	Difference in means of cluster summaries of proportion of persons of all ages slept under any net night before survey between arms
Population	Total population size of larger trial arm no more than 10% larger than smaller arm	Enumeration datasets	Sum (pop size of clusters arm large)/sum (pop size of clusters arm small) less than 1.10
Urbanization^a^	Number of urban clusters in each arm nearly balance	Census data using national classification (alternatively remotely sensed classification could be used (GRUMP/WorldPop))	*N* in arm A ± 1 of *N* in Arm B
Housing density^a^	Difference in mean housing density between trial arms ≤ 0.3 SD of overall cluster level housing density	Enumeration + cluster boundaries GIS files Or Remote sensed data (GRUMP/WorldPop) plus Cluster boundaries GIS	SD (cluster estimates of housing densities) × 0.3 ≥|mean (cluster estimates housing density Arm a) – mean (cluster estimates of housing density Arm b)|
HF location	Number of clusters with a primary care facility nearly balanced across arms	Study team documentation	*N* in arm A ± 1 of *N* in Arm B
Altitude	Differences in mean altitude of cluster centroids between trial arms ≤ 0.3 SD of overall cluster level mean altitude	Digital Elevation Model (ASTER) combined with (GIS) shape files for cluster boundaries	SD (cluster estimates of altitude) × 0.3 ≥|mean (cluster estimates of altitude Arm a) – mean (cluster estimates of altitude Arm b)|
Entomological data collection	Number of clusters with entomological data collection planned is exactly equal across study arms	Study team self-report	*N* in arm A = *N* in arm B

^a^Either urbanization or housing density will be selected; these variables are likely collinear

After allocation, the intervention will be implemented in the entire ATSB arm according to the assignment. Allocation of study arms will not be blinded to the participants, the deliverers of the intervention, or the main investigators (but will be to lab workers carrying out tests on blood samples and mosquitos). Sham bait stations will not be used in control areas.

### Sample size

Full details of the sample size calculations are contained in the trial master protocol and study site-specific protocols; the sample size determination is presented here in summary form (Tables 2, 3, and 4).

**Table 2 Tab2:** Sample size for incidence

	Mali	Kenya	Zambia
Clusters per arm (overall)	38 (76)	35 (70)	35 (70)
Trial duration in calendar years (seasonality of FU) (total FU per participant time in months)	2 years (8-month seasons) (16 months FU)	2 years (12-month seasons) (24 months FU)	2 years (6-month seasons) (12 months FU)
α (type 1 error probability for 2-year trial)	0.05 (Haybittle-Peto with one interim analysis)	0.05 (Haybittle-Peto with two interim analyses at approx. 50% and 75%)	0.05 (Haybittle-Peto with one interim analysis)
Power	88%	80%	80%
Baseline incidence of clinical malaria in the target age group	0.40 events per person-year (based on 0.6 incident events during an 8-month malaria season) (5y– < 15y)	0.845 events per person-year during a 12-m malaria transmission season (1y– < 15y)	0.50 events per 6-month malaria season (Jan–Jun) (1y– < 15y)
Reduction in baseline incidence (incidence rate ratio = 0.70)	30%	30%	30%
Coefficient of variation	0.40	0.40	0.40
Assumed loss of person time, including true LTFU plus loss due to exclusion of person time following each treatment with AL	20%	20%	34%
Total person-years required (number enrolled per cluster before loss-to-follow-up)	3850 person-years (obtained by enrolling 38 individuals per cluster to account for loss-to-follow-up, followed for a total of 16 months)	1260 person-years (obtained by enrolling 13.5 individuals per cluster to account for loss-to-follow-up, followed for a total of 24 months)	1610 person-years (obtained by enrolling 35 individuals per cluster to account for loss-to-follow-up, followed for a total of 12 months)

**Table 3 Tab3:** Sample size for prevalence outcomes

	**Mali**	**Kenya**	**Zambia**
Cluster per arm	38	35	35
α (2-tailed)	0.05	0.05	0.05
Power	90%	80%	90%
Baseline parasite prevalence measured by RDT among participants aged 6 months and older	50%	29.0%^a^	50.0%
Reduction in baseline prevalence	30%	30%	30%
ICC = intracluster correlation coefficient (coefficient of variation)	0.16 (cv = 0.4)	0.05	0.10
Non-response	20%	20%	20%
Sample size per cluster (accounting for non-response)	25 (32)	24 (30)	16 (20)
Total sample size per survey round/year (accounting for non-response)	1900 (2432)	1680 (2100)^b^	1120 (1400)

^a^Prevalence estimates are for individuals aged ≥ 1 month (Kenya only)

^b^Per year in Kenya as trial uses a continuous survey approach

**Table 4 Tab4:** Sample size and power characteristics of each trial for entomological measures

	**Kenya**	**Zambia**	**Mali**
Clusters per arm	8 (16 total)	10 (20 total)	15 (30 total)
α	0.05 (two-tailed)	0.05 (two-tailed)	0.05 (two-tailed)
β	0.20 (> 80% power)	0.20 (> 80% power)	0.20 (> 80% power)
Number of months of sampling per cluster	12	8	24
Number of sampling sites (households) per cluster per month	10	10	10

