## Case incidence cohort

The sample size calculations for the case incidence cohort were calculated using the formula for cluster randomized trial event rates with a person-time denominator [5]. Assumptions utilized in the calculations are summarized below. These assumptions are based on data from similar studies conducted in comparable settings for each study site. In each case, the calculation was completed for the person-time required to demonstrate superiority with a 30% reduction in cumulative clinical case incidence of malaria over a 2-year period. Note that cohort follow-up time differs across the sites. A seasonal cohort will be implemented in Mali (8 months of follow-up per study year) and Zambia (6 months of follow-up per study year). In Kenya, the cohort study will run continuously for the 2-year period,however, the cohort will be rotated every 6 months (i.e., each individual will be followed for up to 6 months) in the first year but will not be rotated (e.g., each individual will be followed for 1 year in the second year).

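### Kenya's 13.5 individuals enrolled per cluster with 24 months of follow-up cannot be squared with its rotating cohort, and the cell does not reproduce its own 1260 person-years

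*SAP article*

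**What the plan says.** Table 2 (SAP article, Sample size) has a row for follow-up, defined as "total FU per participant time in months". The Kenya entry is "2 years (12-month seasons) (24 months FU". The last row, headed as total person-years required with the number enrolled per cluster before losses, gives Kenya "1260 person-years (obtained by enrolling 13.5 individuals per cluster to account for loss-to-follow-up, followed for a total of 24 months". The same table gives Kenya 35 clusters per arm (70 in all), 80% power, a 20% loss of person-time, 0.845 control events per person-year, an incidence rate ratio of 0.70 and a coefficient of variation of 0.40.

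The Case incidence cohort section says that Kenya observes continuously for two years but that "the cohort will be rotated every 6 months (i.e., each individual will be followed for up to 6 months) in the first year", whereas in the second year it "will not be rotated (e.g., each individual will be followed for 1 year in the second year".

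The section on statistical interim analyses adds a third figure for Kenya: 829 primary events expected in the control arm over two years. The event triggers of 415 and 622 are 50% and 75% of that number.

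**The concern.** Two statements about the same people conflict. Table 2 has Kenya participants followed for 24 months; the cohort section allows each person at most 6 months in year 1 or 12 months in year 2. A headcount of 13.5 per cluster that relies on 24 months per head therefore cannot be the number enrolled. The person-years figure beside it does not follow from the headcount either, and the event count used for the interim analyses rests on yet another amount of person-time.

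Three things depend on these figures. The first is the recruitment target for Kenya, where the table's number is too low by a factor of about 2.5 to 3. The second is a reader's ability to tell which person-time the stated 80% power belongs to. The third is the interim triggers, which fire on person-time or on events, whichever comes first, and so need both on one basis.

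**Working it through.** **Inputs.** All come from Table 2 except the rotation (Case incidence cohort section) and the 829 events (interim-analysis section): 70 clusters; 13.5 individuals per cluster; 24 months; 20% loss; λ0 = 0.845 and λ1 = 0.845 × 0.70 = 0.5915 per person-year; k = 0.40; two-sided alpha 0.05.

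**1. The plan's own figure.** Person-years = clusters × individuals per cluster × years × (1 − loss).
- Mali: 76 × 38 × 16/12 = 3851 gross (stated 3850).
- Zambia: 70 × 35 × 1 × 0.66 = 1617 net (stated 1610).
- Kenya: 70 × 13.5 × 2 = 1890 gross; 1890 × 0.80 = 1512 net. Stated: 1260.

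Mali reproduces on a gross basis and Zambia on a net basis. Kenya reproduces on neither. To reach 1260 the loss would have to be 1 − 1260/1890 = 33.3%. At the stated 20%, 1260 needs 1260/(70 × 2 × 0.80) = 11.25 individuals per cluster under observation.

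**2. Distinct individuals under rotation.** Two 6-month groups followed by one 12-month group make three groups filling the same places.
- 13.5 places: 3 × 13.5 = 40.5 per cluster, or 2835 in total against 70 × 13.5 = 945 (factor 3.0).
- Sized to 1260 person-years at 20% loss: 3 × 11.25 = 33.75 per cluster, about 2363 in total (factor 2.5).
- If the second group were carried into year 2, 13.5 places would take 27 individuals (factor 2.0), but that conflicts with the 6-month limit.

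**3. Power by person-time.** The SAP names a cluster-trial formula for rates but does not print it. I assume the standard form, with y person-years per cluster and c clusters per arm:

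c = 1 + (z_α/2 + z_β)² × [(λ0 + λ1)/y + k²(λ0² + λ1²)] / (λ0 − λ1)²

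Solved for power: Φ(√{(c − 1)(λ0 − λ1)² / [(λ0 + λ1)/y + k²(λ0² + λ1²)]} − 1.96).

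With c = 35, (c − 1)(λ0 − λ1)² = 34 × 0.06426 = 2.185, λ0 + λ1 = 1.4365, and k²(λ0² + λ1²) = 0.1702.
- 1260 person-years: y = 18; bracket 0.0798 + 0.1702 = 0.2500; √8.739 = 2.956; power 84.0%.
- 1512 person-years: y = 21.6; bracket 0.0665 + 0.1702 = 0.2367; √9.230 = 3.038; power 86.0%.
- 80% power needs y = 13.3, about 930 person-years. At y = 13.5 (945 person-years) power is 80.3%, so 13.5 fits person-years per cluster better than a headcount. That is only a possible origin of the number.

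**4. Expected control-arm events.** Events = control-arm person-years × 0.845.
- 1260 in total: 630 × 0.845 = 532.
- 1512 in total: 756 × 0.845 = 639.
- 829 events: 829/0.845 = 981 control-arm person-years, about 1960 in total. Per cluster that is 981/35 = 28.0 person-years, or 14 places occupied for two years with no deduction for loss.

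Against 532 expected events, the second trigger of 622 would not be expected to be reached. Against 639 it would come at 622/639 = 97% of the person-time.

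**The case against.** The best defence is that the calculation was done in person-time, which does not depend on how many different people supply it. The rotation is openly described, and the article refers readers to the master and site protocols for full sample-size details. The count of distinct individuals across rotations is a recruitment figure that such an article may leave to those documents. The gap between 1512 and 1260 is a surplus over what is said to be required.

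Much of this stands. Deferral to the protocols excuses an omission. It does not excuse a stated number that contradicts another statement in the same article: the table's labels say per participant and enrolled, and nothing in it refers to places.

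A reader might go further and infer that the Kenya trial is underpowered. If 13.5 people per cluster were enrolled once and never replaced, the average follow-up would be (6 + 6 + 12)/3 = 8 months. That gives 70 × 13.5 × 8/12 × 0.80 = 504 person-years and about 68% power. The documents do not support that reading. The cohort runs continuously and is rotated, which means places are refilled. The event count says the same: even with a full year each and no losses, 13.5 people per control cluster would yield only 35 × 13.5 × 0.845 = 399 events, less than half of 829.

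Nor do the documents establish 40.5 as the correct enrolment. It rests on reading 13.5 as concurrent places, and the article does not say whether someone may be drawn again at a later rotation.

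**Conclusion.** The point holds as an error in stated figures, not as a loss of power. Table 2's 24 months per participant is incompatible with the rotation, and 13.5 cannot be the number of distinct individuals enrolled per cluster. Assuming three successive groups of different people, the number is about 40 per cluster for 13.5 refilled places, or about 34 if sized to 1260 person-years at 20% loss.

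Independently of the rotation, the Kenya figures imply three different totals: 1260 as stated, 1512 (1890 gross) from the cell's own inputs, and about 1960 from the expected events. The stated 80% power matches none of them. The power figures assume the standard formula, with the control rate, effect and between-cluster variation at their Table 2 values and no allowance for the interim looks. With places refilled, each total exceeds the power claimed.

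**What to change.** Reconcile Table 2, the Case incidence cohort section and the interim-analysis section for Kenya. In the Kenya cell, state:
- the number of concurrent places per cluster;
- the number and length of the successive cohorts;
- the resulting number of distinct individuals, and whether anyone may be sampled again;
- follow-up per individual of 6 or 12 months in place of 24.

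Then give one net person-years figure, with the loss assumption that produces it, and restate the power and the expected control-arm events (and hence the event triggers) on that same basis. The sponsor should supply the intended numbers from the original calculation; the 34 to 40 range above is a check on them, not a replacement. If the intended design is refilled places, nothing in the conduct of the trial need change for the table. The cost is a correction to one column of Table 2 and, if the 829 is revised, to the trigger counts.

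If the triggers change, this should be settled without sight of results by arm.
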